## 4.2 Intervention

### Intervention:

The intervention in this study is the place of care, the exact same care is given but in SSC with a parent or surrogate instead of resuscitator or incubator. This will be continuous for the first six hours of life, and as much as possible during the first 72 hours.

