### 6.2 Secondary endpoints

The time points below are the *corrected age* of the infant, calculated from expected date of full-term birth (not the chronological age calculated from actual date of premature birth). For some secondary outcomes only a subsample of infants will be studied.

Respiratory function: Need for surfactant, number of days in ventilator, number of days in CPAP, number of days requiring oxygen.

Heart rate variability: Postpartum, after 48-72 hours, at discharge and at 3-4 months.

Thermal regulation: Axillary temperature is measured continuously, alternatively every hour on infant, and if in SSC also on parent.

Infections: Proportion of infants that experience sepsis during admission in the neonatal ward according to case record, and total number of days treated with antibiotics.

Breastfeeding, nutrition, and growth: Age at first feed, age at first passage of meconium, time to full enteral feeding, time to weaning from feeding tube, lowest weight, time to return to birth weight, weight gain in grams per day during admission, and weight at discharge as well as term age as per case record. Nutrition and breastfeeding status will be completed weekly according to the Index of Breastfeeding Status (IBS) questionnaire during hospital stay, at discharge, at term age, at 3-4 months of age and at 12 months. The Breastfeeding Self-Efficacy Questionnaire (BSES) will be completed at 7 days, 3-4 months, and the Infant Breastfeeding Assessment Tool (IBFAT) each week during admission, at discharge, at term age and at 3-4 months.

Epigenetics: Whole genome analysis as well as locus specific methylation of stress related genes for Oxytocin receptor (OXTR), glucocorticoid receptor (NR3C1), Arginine-vasopressin receptor (AVP), Proopiomelanocortin (POMC), Glutamate decarboxylase-1 (GAD1), Glutamate receptor (GRM1), Brain-Derived Neurotrophic Factor- (BDNF), serotonin transporter (SLC6A4 och SERT), serotonin receptor (5H2A) och serotonin degradation enzyme (MAOA) in cord blood postpartum, in buccal swabs postpartum and at 6 hours, whole blood from opportune time during first 6 hours, whole blood and buccal swabs at 48-72 hours, at 3-4 months and at 24 months of age.

Microbiota: Infant colonization by microbiome (bacteria) is identified by DNA analysis from fecal samples at 0-6 hours, 72 hours, 3-4 months, 12 och 24 months, and compared to the parents. Vaginal, rectal, and skin samples from mother and partner are collected at 0-6 hours.

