### As soon as possible after birth:

- Cord blood and buccal swab is taken from the infant for epigenetic testing.
- Fecal sample and skin swab taken from the infant for analysis of microbiota
- Maternal samples from rectum, vagina and skin for microbiota analysis.
- Father or partner swabbed for microbiota analysis.
- HRV

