### At 6 hours of age

- Buccal swab is taken from the infant for epigenetic analysis.

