(MAOA) i cord blood postpartum, in buccal swabs postpartum. Midwife or nurse in labour ward collect cord blood concomitant with routine collection. Neonatal nurse collects blood samples at the same time as required clinically, as well as buccal swab during hospital stay or at follow-up visit. Samples are transported to the Unit for "Medicinsk Epigenetik, Centrum för Molekylärmedicin", KI. Analysis is undertaken by responsible researcher.

Microbiota: Infant microbiome colonization is identified with DNA analysis from fecal samples and skin swabs, and compared to that of their parents. Samples from infant are collected by ward nurse. Tests from parents are collected by nurse, or by the parents themselves. Samples are sent to the Center for Translational Microbiome Research (Molekylär- och Tumörbiologiskt Centrum; MTC).

Brain function maturation: EEG is measured with 8 leads using existing apparatus in clinical use. The results will be interpreted by the Nurture Science Programme, Columbia University, NY.

Structural maturation of brain: MR brain will be done on a subsample at term age. Results will be interpreted by radiologists.

Attachment: attachment will be assessed by psychologist on films made during the "Still Face-test" as well as the Parent-Child Early Relational Assessment Scale (PCERA). Filming is done by research staff. A psychologist or other appropriately trained staff at Linköping University or Karolinska Institutet will interpret the films.

Brain function: Functional magnetic resonance imaging (fMRI) will examine activation patterns in specific areas on mother's brain while she looks at pictures of her own and other infants in different moods. Parents will be invited to radiology department and the examination conducted by radiologists who will assess whether there are any structural differences, with the hypothesis that functional and structural connectivity in parenting behavior specific areas (e.g. prefrontal cortex and amygdala) are related to time in SSC.

Parental mental health: Experience of care will be assessed in interviews at discharge. Questionnaires Edinburgh Postnatal Depression Scale (EPDS), The Spielberg State-Trait Anxiety Inventory (STAI) and the Swedish Parenthood Stress Questionnaire (SPSQ) are administered. A research nurse distributes the questionnaires and parents complete them during hospital stay or at home before follow-up visit. Proportions are analyzed.

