### **11.2 Statistiscal analysis**

Primary outcome analysis will be done according to intention to treat (ITT) on all subjects that met inclusion criteria without exclusion criteria and were randomized. Per protocol analysis will also be undertaken based on actual adherence to allocated place of care. For safety measures the entire sample will be included. All continuous variables will be described with sample size and number of observations, average and median values, with standard deviations and minimum and maximum values. All categorical variables will be summarized in frequency tables. For the primary outcome a mixed model-regression analysis will be done to evaluate the effect of gestational age, birth order, single or multiple birth, intrauterine growth retardation, mode of birth (vaginal or caesarean), antenatal corticosteroids given or not, and birth weight. The null hypothesis is that there is no difference in the groups for the primary outcome. The analysis will be done for the whole study population as well as those that received the intervention.

An interim analysis will be done for the primary outcome on the first 30 patients enrolled.

Secondary outcomes that are continuous or categorical will be analyzed by linear or mixed model regression models, and dichotomous variables by logistic regression models. Stratification factors utilized in the randomization will be used as covariates. Qualitative and exploratory methods will be used as required.

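### Section 9.1 names only the two birth samples for methylation; cord blood cannot show an effect of skin-to-skin contact and should be defined as a baseline, with 9.1 aligned to 6.2

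*Protocol*

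**What the plan says.** **Section 9.1 (effectiveness, epigenetics).** Whole-genome and locus-specific methylation is to be measured in two named samples; the sentence ends "MAOA) i cord blood postpartum, in buccal swabs postpartum". A later sentence on who collects what mentions blood drawn when clinically required, "as well as buccal swab during hospital stay or at follow-up visit", without time points.

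**Section 6.2 (secondary endpoints).** The same analysis is to be done "in cord blood postpartum, in buccal swabs postpartum and at 6 hours, whole blood from opportune time during first 6 hours", followed by "whole blood and buccal swabs at 48-72 hours, at 3-4 months and at 24 months of age".

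**Section 7.2 (procedures).** At the earliest opportunity after birth, "Cord blood and buccal swab is taken from the infant for epigenetic testing". At 6 hours of age, "Buccal swab is taken from the infant for epigenetic analysis". The later visits repeat the collections listed in 6.2.

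**Section 4.2 (intervention).** On SSC: "This will be continuous for the first six hours of life, and as much as possible during the first 72 hours".

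**Section 11.2 (analysis of secondary outcomes).** "Stratification factors utilized in the randomization will be used as covariates". Baseline methylation is neither named nor ruled out.

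No section calls either birth sample a baseline, and no section specifies a between-arm test on them.

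**The concern.** The summary and section 5.2 ask whether SSC changes the epigenetic profile. A sample can bear on that question only if it is taken after some exposure. The two samples that 9.1 names are the earliest in the schedule and the least able to show an effect, and 6.2 gives them the same standing as the samples that can.

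Two things are at stake. First, if the birth samples are read as effectiveness endpoints, a nominally significant arm difference in cord blood could be reported as an effect although it can only be chance. Section 17 plans a separate publication for each outcome, so how these samples are labelled matters. Second, the infant's own value at birth, which will be collected anyway, has no stated role in the analysis of the later samples, where it could reduce between-infant variation.

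**Working it through.** The protocol gives no sample size, effect size, standard deviation or correlation for the epigenetic outcome, so there is no figure to reproduce. The check compares the sections and then sizes the possible gain under stated assumptions.

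**1. Sample by sample**

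| Sample | 9.1 | 6.2 | Relation to SSC |
|---|---|---|---|
| Cord blood | named | listed | formed before SSC can start |
| First buccal swab | named | listed | probably before SSC; order not fixed |
| Whole blood, first 6 h | no time point | listed | exposure varies with time of draw |
| Buccal swab, 6 h | no time point | listed | after exposure |
| Blood and swab, 48-72 h | no time point | listed | after exposure |
| Blood and swab, 3-4 and 24 months | no time point | listed | after exposure |

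The two sections therefore differ in the samples they name, although 9.1 mentions later collection in general terms.

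**2. Cord blood.** It reflects fetal life. Under randomization the expected difference between arms is zero, provided that missing samples do not depend on arm. A 5% test on it rejects about 5% of the time whatever SSC does. If one were run on each of the ten genes listed (counting SLC6A4 and SERT as one), and the tests were independent, the chance of at least one false positive would be 1 - 0.95^10 = 0.40. This is conditional: the protocol does not specify such tests.

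**3. First buccal swab.** Section 7.2 places it as early as possible after birth, but SSC also starts from birth and no rule puts the swab first. Zero expected difference is therefore likely for the swab but not assured.

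**4. Gain from using the birth value as covariate.** With correlation r between the birth and later values, the residual variance is multiplied by 1 - r². The detectable difference at 80% power, two-sided 5%, with 75 infants per arm is (1.960 + 0.842) × √(2/75) × √(1 - r²) in SD units. At r = 0 this is 2.802 × 0.1633 = 0.457 SD.

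| Assumed r | 1 - r² | Variance removed | Detectable difference (SD) | 150/(1 - r²) |
|---|---|---|---|---|
| 0.1 | 0.99 | 1% | 0.455 | 152 |
| 0.3 | 0.91 | 9% | 0.436 | 165 |
| 0.5 | 0.75 | 25% | 0.396 | 200 |
| 0.7 | 0.51 | 49% | 0.327 | 294 |

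The last two columns assume that all 150 infants contribute. Sections 6.2 and 7.1 say that some outcomes use subsamples, so the absolute figures may not apply. The proportion of variance removed does not depend on the number analysed.

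**The case against.** A reader might infer that the trial cannot answer its epigenetic hypothesis. The documents do not support that. Section 6.2 and the procedures provide samples from 6 hours to 24 months, and 9.1 itself mentions later collection. Section 9.1 also omits time points for other outcomes such as HRV and EEG, which suggests an abbreviated list rather than a decision to judge effectiveness at birth.

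A reader might also infer that false findings in the birth samples are planned. No section specifies an arm comparison on them, and listing the first measurement of a series beside the later ones is ordinary practice.

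A third inference would be that precision is definitely lost. Section 11.2 names the stratification factors but does not say that they are the only covariates, it allows mixed models, and an analysis plan that is not shown may add a baseline term. The correlations are assumptions, and at 0.1 the gain is negligible. Cord blood is also not a like-for-like match for later infant whole blood. If the first swab were taken after SSC had begun, adjusting for it would mean adjusting for a value that the intervention may already have changed.

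These points all stand and limit the finding. They leave two facts untouched: 6.2 and 9.1 do not name the same samples, and cord blood is listed under endpoints and effectiveness with no baseline role. Whether a sample is an endpoint or a baseline is part of the endpoint definition, which the protocol itself sets out in these two sections.

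**Conclusion.** The point holds in a limited form and is minor. Section 9.1 should be reconciled with 6.2. Cord blood cannot serve as an effectiveness sample, because its expected arm difference is zero; the first buccal swab probably cannot either, but that depends on a sampling order which the protocol does not fix. The epigenetic hypothesis remains testable with the later samples.

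Using the birth value as a covariate would be better than the covariate set that 11.2 states, but its size cannot be derived from the documents: 1% to 49% less residual variance over assumed correlations of 0.1 to 0.7, in whatever subsample is analysed. Epigenetic profile is among the stated aims, but it is one of many secondary hypotheses, and 9.3 describes many outcomes as exploratory. Neither the primary outcome nor safety is affected.

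**What to change.** - **Section 9.1:** replace the two-sample list with the schedule in 6.2, or refer to 6.2.
- **Sections 6.2 and 9.1:** name the post-exposure samples as the effectiveness endpoints. For blood drawn in the first 6 hours, record the time of the draw, since exposure will vary.
- **Birth samples:** define cord blood as baseline. Define the first buccal swab as baseline where it is taken before SSC starts, and record the order of swab and SSC for each infant. Run no arm-effect test on baseline samples.
- **Section 11.2 or the analysis plan:** add the birth buccal value, where it qualifies as baseline, as covariate for later buccal results. Add cord blood as covariate for later whole-blood results, acknowledging that the match is imperfect.

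The cost is wording, one recorded item on sampling order, one extra model term, and a stated way of handling missing birth samples (imputation or a missing-value indicator). No additional sample is needed.

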## **9.2 Assessment of clinical safety**

Study sponsor will be informed on unexpected and adverse events, their nature, their frequency, and number of study subjects, collated monthly. Serious adverse events (SAE) shall be reported to sponsor within 24 hours. Evaluation is done as described in section 10 (below), only respiration, temperature and infection parameters will be assessed as to clinical safety. Any SAE shall be reported within one week to the Data Safety Monitoring Board (DSMB), who will also receive outcome reports every 6 months to detect any possible large or clinically important difference in the study groups.

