## **METHODS**

Study design: randomized controlled trial.

Duration: Continuous skin-to-skin contact with any parent during the first six hours of life, and as much as possible the first three days.

Primary hypothesis: Does cardiorespiratory stabilization improve?

Effectiveness outcomes: all other outcomes.

Safety parameters: respiration, thermal control, infections.

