### 10.3 Methods to discover adverse events

Adverse events are:

- Death
- Cardiorespiratory deterioration with need for increased intensive care, for example apnea obs vi har ett stavfel högre upp with need for ventilation, circulatory collapse with need for bolus fluids and inotrope treatment. Acquired infections.
- Intraventricular haemorrhages
- Nil per mouth due to suspected necrotizing enterocolitis.
- Other conditions requiring transfer to higher level of care.

Of the above examples, death and any condition with risk of death and prolonged hospital care and future disability are categorized as severe adverse events.

A Data Safety Monitoring Board (DSMB) will oversee the study and its data independently. The DSMB will be chosen to include competence in neonatology, epidemiology, global health, and biostatistics. The DSMB will receive quarterly reports from a statistician on safety data. Based on this the DSMB can recommend pausing study enrollment, modify the study intervention or stop the study.

Investigator, co-investigators, and research nurses will within 24 hours report all serious adverse events to sponsor, and all adverse events on a monthly basis. The sponsor will inform the DSMB within one week of a serious event and collated every 6 months for adverse events.

An interim analysis is planned after 30 subjects have been enrolled.

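### The safety assessment is confined to respiration, temperature and infection, so death, circulatory collapse, intraventricular haemorrhage and suspected necrotizing enterocolitis fall outside the trial's stated safety conclusion

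*Protocol*

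**What the plan says.** Three parts of the protocol bear on which harms count as safety outcomes.

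- Section 1 (Summary, Methods): "Safety parameters: respiration, thermal control, infections".
- Section 9.2: the relevant sentence begins "Evaluation is done as described in section 10 (below" and then says that "only respiration, temperature and infection parameters will be assessed as to clinical safety". The section also sends serious events to the DSMB within one week and gives the DSMB outcome reports every six months, meant to reveal marked differences between the groups.
- Section 10.3: the adverse events are death, cardiorespiratory deterioration (including circulatory collapse), acquired infections, "Intraventricular haemorrhages", "Nil per mouth due to suspected necrotizing enterocolitis", and other conditions that lead to transfer to a higher level of care. Of these, "death and any condition with risk of death and prolonged hospital care and future disability are categorized as severe adverse events".

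On DSMB timing, section 10.3 says "The DSMB will receive quarterly reports from a statistician on safety data". Its next paragraph has the sponsor inform the DSMB of serious events within one week, and "collated every 6 months for adverse events".

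Section 6.2 covers surfactant, ventilator, CPAP and oxygen use, temperature, sepsis and antibiotic days. It does not include death, intraventricular haemorrhage or necrotizing enterocolitis. Section 11.2 says that safety measures are analysed on the entire sample but does not say what those measures are.

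**The concern.** The sentence in 9.2 is a stated restriction, not a detail left open. With the word *only* in it, an analysis plan that treated death or intraventricular haemorrhage as safety outcomes would depart from the protocol. The same sentence hands evaluation to section 10, which is wider, so its two halves cannot both be followed.

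This matters because of what the trial is meant to deliver. Section 4.3 gives the safety of the method as part of the aim. Section 14.3 expects the results either to support wider use or to check a trend towards skin-to-skin care of smaller and sicker infants. The background in 4.2 presents mortality as a main effect of this form of care. A safety conclusion built on three domains, with the gravest recorded events outside it, could reassure more than the data allow.

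A smaller matter is that the DSMB's periodic reports on safety data and on adverse events are given different intervals within one section, although adverse events are safety data.

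**Working it through.** The plan gives no figure to reproduce here. The main check is textual; the arithmetic shows how precise a comparison could be.

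**1. Events in 10.3 against the three safety domains**

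| Event in 10.3 | In a domain of 1 and 9.2? | Endpoint in 6.2? |
|---|---|---|
| Death | No | No |
| Apnoea needing ventilation | Respiration | Partly (ventilator days) |
| Circulatory collapse | No | No |
| Acquired infection | Infection | Sepsis, antibiotic days |
| Intraventricular haemorrhage | No | No |
| Suspected necrotizing enterocolitis | No | No |

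Four listed events lie outside both the safety domains and the endpoints.

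**2. Are they recorded and seen?** Yes. Sections 10.4.1 and 11.1 put all adverse events in the CRF, and 10.5 requires every event and its outcome to be documented. Serious events go to the sponsor within 24 hours and to the DSMB within one week (9.2 and 10.3).

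**3. Precision with 75 per arm (section 7.1)**

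- No events in one arm: upper limit of the two-sided 95% interval = 1 − 0.025^(1/75) = 4.8%.
- Half-width of the 95% CI for a risk difference when both arms have risk p: 1.96 × √(2p(1 − p)/75). The protocol gives no expected rates, so p is an assumption:
  - p = 5%: 1.96 × √(2 × 0.05 × 0.95/75) = 7.0 percentage points
  - p = 10%: 1.96 × √(2 × 0.10 × 0.90/75) = 9.6 percentage points
  - p = 20%: 1.96 × √(2 × 0.20 × 0.80/75) = 12.8 percentage points
- Mortality, for context: section 4.2 cites 3.2% against 5.3% (3.2/5.3 = 0.60, matching the cited RR). In 75 infants that is 75 × 0.032 = 2.4 against 75 × 0.053 = 4.0 expected deaths. The usual normal approximation for two proportions (two-sided 0.05) gives about 9% power with 75 per arm, and about 1,448 per arm for 80%.

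Any comparison of these events would therefore be descriptive.

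**4. DSMB reports**

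| Place | Content | Sender | Interval |
|---|---|---|---|
| 9.2 | Outcome reports | Not stated | 6 months |
| 10.3 | Safety data | Statistician | Quarterly |
| 10.3 | Adverse events | Sponsor | 6 months |
| 9.2, 10.3 | Serious events | Sponsor (10.3) | Within 1 week |

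The second and third rows overlap in content. Enrolment from 1 May 2017 to 31 October 2020 is 42 months, so 42/3 = 14 quarterly or 42/6 = 7 half-yearly reports. At even accrual, 150/42 = 3.57 infants a month, or 3 × 3.57 = 10.7 against 6 × 3.57 = 21.4 infants between reports. Accrual was not designed to be even, since Huddinge joined only in November 2018 (4.2). The contrast concerns periodic summaries and events not classed as serious.

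**The case against.** The strongest reply is that the three domains are only the prespecified safety parameters, with adverse events handled in full under section 10, as 9.2 itself indicates. Adverse events are often reported apart from endpoints, and section 11.2 promises frequency tables for all categorical variables. Final adverse event tables by arm are ordinary content of a statistical analysis plan, which is not at hand.

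Much of this stands. The absence of a table specification is not a fault in itself, nor is the absence of these events from 6.2 taken alone. What remains is that 9.2 positively excludes other parameters from the safety assessment and section 1 repeats the list. An analysis plan cannot widen that without contradicting the protocol.

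Three stronger readings are tempting but not supported:

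- *These events are never compared between arms.* The six-monthly DSMB reports in 9.2 are meant to find group differences, so comparison during the trial is foreseen. What is not named is a comparison in the final analysis.
- *The DSMB would learn of the gravest events late.* The one-week rule for serious events rules this out for deaths and life-threatening events. Only an event such as a haemorrhage or suspected enterocolitis that is not classed as serious would depend on the periodic reports.
- *Sections 9.2 and 10.3 contradict each other on the DSMB interval.* Outcome reports and safety reports can be separate streams. The unclear point is the overlap inside 10.3, and even there the two items have different senders.

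Low power is a fair caution against testing these events, but no reason to leave them out of a descriptive summary.

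**Conclusion.** The point holds as a conflict between stated rules. Sections 1 and 9.2 confine the safety assessment to three domains, while section 10.3 lists four kinds of grave event outside them: death, circulatory collapse, intraventricular haemorrhage and suspected necrotizing enterocolitis. None is an endpoint, and no final by-arm comparison of them is named in a trial that sets out to establish safety. The consequence falls on the final safety conclusion, not on detection or DSMB oversight. No data are lost, because the events are already collected.

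The size is limited by the sample. With 75 per arm, even no events in one arm leaves a risk of up to about 4.8% open, and for assumed event risks of 5% to 20% the difference would be known only to within about 7 to 13 percentage points. These figures describe what a comparison could show; they do not measure harm from the wording.

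The DSMB timing is a lesser, separate inconsistency, confined to the overlap between quarterly safety data and six-monthly adverse events in 10.3. The change should be made, at modest priority and low cost.

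**What to change.** 1. In section 9.2, remove the restriction to three domains. Align sections 1, 9.2 and 11.2 with 10.3, so that death, circulatory collapse, intraventricular haemorrhage and suspected necrotizing enterocolitis count as safety outcomes alongside respiration, temperature and infection.
2. In section 11.2, state that these events are summarised by allocated arm on the entire sample, with counts, risk difference and 95% CI, as description without formal testing. Table layouts can stay in the statistical analysis plan. Add a sentence that few or no events would not show absence of risk at this sample size.
3. In section 10.3, reconcile the quarterly safety data with the six-monthly adverse event collation, and say how both relate to the six-monthly outcome reports in 9.2. Give one interval, content and sender for each type of report. The intervals are for the sponsor to choose; the documents do not favour one.

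The cost is amended wording, a few extra tables from data already on the CRF, and a little more reporting work. No new data collection is needed.
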